## 7.5 Reconstitution and Administration of CPI-613

CPI-613 must be diluted from 50 mg/mL to 12.5 mg/mL with 5% Dextrose Water or D5W (i.e., 1 portion of CPI-613 diluted with 3 portions of D5W) prior to administration. The diluted drug product should be visually inspected for clarity. If haziness, precipitate or coloration (other than colorless) is observed, do not use the diluted drug product for dosing. After dilution with sterile D5W, the solution is clear and has a pH of 8.4-8.8. The diluted CPI-613 drug product has been found to be stable for 24 hrs at room temperature and refrigeration temperature (Studies STA-010).

CPI-613 must be administered IV, via an IV catheter that is free flowing and free of air in the dead space of the IV catheter, to minimize vascular irritation, inflammation and acute toxicity of CPI-613 (Study NCL-049). Accidental co-administration of extra air in the dead space of IV catheters during administration of CPI-613 has demonstrated the potential to induce acute toxicity of CPI-613 according to animal studies (Study NCL-049). Also, accidental leakage of CPI-613 into the perivascular space during IV administration, which prolongs exposure of perivascular tissue to CPI-613, can induce significant local inflammation according to animal studies (Studies NCL-027 and NCL-030). To avoid local reactions at and around the site of administration, CPI-613 must be administered via a central venous catheter.

CPI-613 must not be administered as a bolus, but by infusion, at a rate of ~0.5 mL/min, via a central venous catheter with D5W running at a rate of about 125-150 mL/hr. This is to minimize potential acute toxicity of CPI-613, according to animal studies (Study NCL-049) and requires a double lumen Port a Cath.

The following precautions must be taken when administering CPI-613:

A. Confirmation of the placement of the IV line to ensure a lack of leakage of CPI-613 into the perivascular space.

B. Confirmation that the IV line is free flowing.

C. Confirmation that the IV line is free of dead air space.

D. Dilute CPI-613 drug product with D5W, as instructed in the study protocol.

E. Administer CPI-613 by infusion, not as a bolus.

F. After administration of CPI-613, flush the IV line with ~10 mL of D5W to remove residual CPI-613.

G. To avoid local reactions at and around the site of administration, CPI-613 should be administered via a double lumen central venous catheter.

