## 1.2 CPI-613

CPI-613 is a novel anti-cancer agent (Zachar et al. 2011). CPI-613 selectively targets the altered form of mitochondrial energy metabolism in tumor cells, causing changes in mitochondrial enzyme activities and redox status, which leads to apoptosis, necrosis and autophagy of tumor cells (Zachar et al. 2011). The activities of CPI-613 involve the catalytic and regulatory functions of the altered form of the pyruvate dehydrogenase complex (PDC) and the α-ketoglutarate dehydrogenase complex (KGDHC) found in tumor cells (Zachar et al. 2011). Due to its novel mechanism of action and the multi-molecular targeting approach, CPI-613 is equally effective against multi-drug resistance (MDR) cancer cell lines when compared to the parental untreated cancer cell lines, according to *in vitro* studies (Zachar et al. 2011).

According to Phase I dose-escalation trials in patients with various advanced stages of solid and hematologic malignancies, CPI-613 is well-tolerated at doses up to 3,000 mg/m^2^ when infused intravenously over two hours. CPI-613 also exhibits anti-tumor activities in these patients (Pardee et al, 2011a and b, & 2012; Lee et al. 2011 & 2012; Senzer et al 2012), even in the Phase 1 patient population were those with relapsed or refractory disease.

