| * Cycle Length is 4 weeks, with treatment on Days 1 and 4 of Weeks 1 through 3; week 4 is a rest  week (no treatment)  ** The only pre-study data that will be used for data analyses are ECOG status, baseline CT or PET/CT, and LDH. See section 5.1.4 for details.  a: Pre-study requirements must be completed **within** **the following time**  **frames:**  Within **4** weeks: tumor assessments based on contrast CT of chest and abdomen or PET/CT;  Within **2** weeks: medical history, physical exam, vital signs, height, weight, ECOG, evaluation of symptoms and medications, clinical chemistry, hematology, LDH  Within **1** week: pregnancy test for women of childbearing potential  b: Specific chemistries are listed in section 5.2.2. Renal function will be assessed using the Cockcroft-Gault formula.  c: Serum pregnancy test for women of childbearing potential  d: These tests are performed with results available for review within 24 hours before administration of CPI-613  e: CPI-613 is given as a 2-hr IV infusion via a central venous catheter. Treatment with CPI-613 may be adjusted +/- 1 day.  f: Imaging performed while on treatment should be preferably obtained on day 3, 4, or 5 of week 4 during cycles 2, 4,  6 and every two cycles thereafter until progression.  g: Survival and post-study cancer treatment will be monitored bimonthly via telephone contact by the study PA after  patients are taken off of the trial. Phone contact will continue indefinitely.  h: Physical exam and clinical evaluation to be completed within 72 hours prior to treatment with CPI-613 | | | | | | | | | |

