**Table 6-1: Administration of CPI-613 in Patients with Extensive Small Cell Lung Carcinoma**

| **Treatment Cycle** | | | **Administration of CPI-613** |
| --- | --- | --- | --- |
|  | **Week** | **Day** |  |
| **Cycle 1**  **(4 weeks)** | 1 | 1 | 2-hr IV infusion via a central venous catheter |
|  |  | 4 | 2-hr IV infusion via a central venous catheter |
|  | 2 | 1 | 2-hr IV infusion via a central venous catheter |
|  |  | 4 | 2-hr IV infusion via a central venous catheter |
|  | 3 | 1 | 2-hr IV infusion via a central venous catheter |
|  |  | 4 | 2-hr IV infusion via a central venous catheter |
|  | 4 |  |  |
| **Cycle 2**  **(4 weeks)** | 1 | 1 | 2-hr IV infusion via a central venous catheter |
|  |  | 4 | 2-hr IV infusion via a central venous catheter |
|  | 2 | 1 | 2-hr IV infusion via a central venous catheter |
|  |  | 4 | 2-hr IV infusion via a central venous catheter |
|  | 3 | 1 | 2-hr IV infusion via a central venous catheter |
|  |  | 4 | 2-hr IV infusion via a central venous catheter |
|  | 4 |  |  |
| Etc. until progression |  |  |  |

hr = hour; IV = intravenous; min = minutes.

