## 6.1 Sample Size, Dose Levels and Justification of the Dose

The sample size will be 20 for this pilot trial.

This study will use the maximum tolerated dose (MTD) established in the study conducted by Pardee and colleagues (CCCWFU 29109; IRB00012124). This MTD for single-agent use of CPI-613 infused over 2 hours is 3,000 mg/m^2^.

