## 6.2 Adverse Event-Related Dosing Delay and Dose Modification

For adverse events unrelated to serum creatinine elevation or reduction in renal function but are possibly related to CPI-613, the occurrence of Grade 1 toxicity does not generally require dose modification for subsequent doses for that patient. However, if Grade 2 toxicity (other than alopecia and nausea) probably related to CPI-613 develops, treatment is to be withheld and can resume only after the Grade 2 toxicity has been reduced to Grade 1 or below, and the dose level for subsequent doses for that patient will be reduced by 25% of the dose at which such Grade 2 toxicity occurs. Grade 2 alopecia and nausea do not require withholding treatment or dose reduction. If Grade 3 or 4 toxicity probably related to CPI-613 develops, dosing of CPI-613 of that patient will be withheld and the patient shall be monitored for recovery from, and reversibility of, such Grade 3 or 4 toxicity. To resume treatment with CPI-613 for a patient who has had CPI-613-related Grade 3 or 4 toxicity, the Grade 3 or 4 toxicity must be reduced to Grade 1 or below, and the dose level for subsequent doses for that patient will be reduced to 50% of the dose at which such Grade 3 or 4 toxicity occurs.

For adverse events related to creatinine elevation or reduction in renal function that are possibly related to CPI-613, dosing of the patient will be withheld if the severity level is Grade 1 or above. Treatment can resume only after the toxicity has been reduced to Grade 0. The dose level for subsequent doses for that patient will be reduced by 15% if the severity level is of Grade 1, by 25% for Grade 2 toxicity, and by 50% for Grade 3 or 4 toxicity.

Furthermore, if the toxicity possibly related to CPI-613 is acute renal failure and the severity level is Grade 3 or 4, further patient enrollment will be temporarily suspended in order to enable assessment of the following aspects of the trial and implementation of corrective measures or protocol amendment, and if necessary:

- compliance of the study sites and investigators to the study protocol

- evaluation of the appropriateness of the procedures for monitoring renal function

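### The infusion rate and dilution required in Section 7.5 cannot deliver 3,000 mg/m² in the stated 2 hours; at adult body size they take about 12 to 18 hours

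*Protocol*

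**What the plan says.** The protocol gives the infusion duration in four places. Section 1.2 reports that CPI-613 was well tolerated at up to 3,000 mg/m² "when infused intravenously over two hours". Section 6.1 adopts the maximum tolerated dose (MTD) from an earlier study: "This MTD for single-agent use of CPI-613 infused over 2 hours is 3,000" mg/m². Footnote e of Table 5-1 says "CPI-613 is given as a 2-hr IV infusion via a central venous catheter", and Table 6-1 enters "2-hr IV infusion via a central venous catheter" for each dosing day.

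Section 7.5 gives the preparation and rate. The drug "CPI-613 must be diluted from 50 mg/mL to 12.5 mg/mL" with D5W before it is given. On the rate it says: "CPI-613 must not be administered as a bolus, but by infusion, at a rate of ~0.5 mL/min". A separate carrier flow of 125 to 150 mL/h of D5W is to run through the central line at the same time. The next sentence of Section 7.5 gives the purpose as limiting acute toxicity and cites an animal study.

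The dose scales with BSA (Section 7.9). Section 6.2 sets percentage reductions for toxicity; the largest applies after Grade 3 or 4 events, when the dose "will be reduced to 50% of the dose at which such Grade 3 or 4 toxicity occurs".

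**The concern.** Once dose, concentration and rate are fixed, the duration follows. Section 7.5 fixes concentration and rate, Section 6.1 fixes the dose, and the tables then state a duration that must agree with the other three. It does not.

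Staff preparing an infusion must break either the rate in Section 7.5 or the 2-hour duration. This matters in three ways.

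- **The basis for the dose.** The MTD was established with a 2-hour infusion. Giving the same dose over half a day or longer is a different regimen, and the MTD does not directly support it.
- **Fluid load.** If the D5W carrier runs throughout a slow infusion, each infusion adds litres of D5W instead of a few hundred millilitres, six times per cycle.
- **Interpretation.** Section 9.0 aims to estimate response, survival and toxicity in 20 patients treated at the MTD. Those estimates need one clearly stated regimen behind them.

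The point is not that either reading exceeds a rate already tested in patients. It is that the protocol does not settle which rate is to be used.

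**Working it through.** **Inputs**

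- Dose: 3,000 mg/m² (Section 6.1)
- Stated duration: 2 h = 120 min (Sections 1.2 and 6.1, Tables 5-1 and 6-1)
- Concentration after dilution: 12.5 mg/mL (Section 7.5)
- Drug infusion rate: about 0.5 mL/min (Section 7.5)
- D5W carrier flow: 125 to 150 mL/h (Section 7.5)
- BSA: not given in the protocol; 1.5 to 2.2 m² is assumed

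**Can the stated 2 hours be reproduced?**

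- Volume per m² = 3,000 / 12.5 = 240 mL
- Time per m² = 240 / 0.5 = 480 min = 8 h
- Rate needed for 2 h = volume / 120

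| BSA (m²) | Dose (mg) | Volume (mL) | Time at 0.5 mL/min | Rate for 2 h (mL/min) | Ratio to 0.5 mL/min |
|---|---|---|---|---|---|
| 1.5 | 4,500 | 360 | 720 min = 12.0 h | 3.0 | 6.0 |
| 1.8 | 5,400 | 432 | 864 min = 14.4 h | 3.6 | 7.2 |
| 2.2 | 6,600 | 528 | 1,056 min = 17.6 h | 4.4 | 8.8 |

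The 2-hour figure is not reproduced.

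**What 2 hours at the stated rate delivers.** 0.5 × 120 = 60 mL, and 60 × 12.5 = 750 mg. That is 750 / 1.5 = 500 mg/m² down to 750 / 2.2 = 341 mg/m², or 17% down to 11% of the intended dose.

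**Dependence on the BSA assumption.** Rate and duration agree where 240 × BSA = 0.5 × 120, so BSA = 60 / 240 = 0.25 m². No adult is that size.

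**Other readings**

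- *Dose halved under Section 6.2:* 180 to 264 mL, so 6.0 to 8.8 h at 0.5 mL/min.
- *Carrier flow taken as the drug rate:* 360 / 150 = 2.4 h to 528 / 125 = 4.2 h. Section 7.5 states this flow separately from the drug rate.
- *Rate taken to mean undiluted 50 mg/mL stock:* 4,500 / 50 = 90 mL to 6,600 / 50 = 132 mL, so 180 to 264 min, or 3.0 to 4.4 h.

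None gives 2 hours across the assumed range.

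**Carrier volume**

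- Slow rate: 12.0 × 125 = 1,500 mL to 17.6 × 150 = 2,640 mL per infusion
- Over 2 hours: 2 × 125 = 250 mL to 2 × 150 = 300 mL

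**The case against.** The best counter-argument concerns the size of the gap. Section 7.5 sometimes uses the drug's name for the 50 mg/mL stock, as in its instruction on mixing proportions. If 0.5 mL/min refers to stock, the diluted solution runs at four times that, 2 mL/min, and the infusion takes 3.0 to 4.4 h: a shortfall of 1.5 to 2.2 times. It is also suggestive that 0.5 × 50 × 120 = 3,000 mg, as if the rate came from a stock-based sum that overlooked BSA. The document does not confirm this. The reading still misses 2 hours, and it sits badly with mandatory dilution before administration. It narrows the gap without closing it.

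A second objection is that the toxicity rationale may support infusion over bolus more than this particular rate. The rationale follows a sentence that covers bolus, rate, catheter and carrier together, and the cited animal study is titled as a comparison of bolus with infusion. This stands in part: nothing in the protocol shows 0.5 mL/min to be a tested safety threshold. The rate is nevertheless part of the instruction that the rationale is given for.

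Third, the 2-hour duration appears repeatedly and the rate once, marked as approximate, so sites may well have infused over 2 hours. That makes the rate the likelier error and lowers the practical risk. It does not make the mandatory instruction workable, and an approximation sign does not stretch to a six- to nine-fold difference.

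Finally, the extra D5W arises only if a site follows the slow rate with the carrier running throughout. It is a conditional consequence.

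**Conclusion.** The concern holds, with high confidence, and must be fixed. On the plain reading, with the rate applied to the diluted solution, Section 7.5 implies 12.0 to 17.6 hours against a stated 2 hours. The hours depend on the assumed BSA range; the contradiction does not. On the stock-rate reading the infusion still takes 3.0 to 4.4 hours.

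The document does not establish which figure is wrong, although the weight of the text and the origin of the MTD favour 2 hours. No harm to patients is claimed, and no size of effect on the response or toxicity estimates is asserted.

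**What to change.** In Section 7.5, replace the fixed rate with: total diluted volume (mL) divided by 120 minutes. Add a worked example:

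| BSA (m²) | Diluted volume (mL) | Rate (mL/min) |
|---|---|---|
| 1.5 | 360 | 3.0 |
| 1.8 | 432 | 3.6 |
| 2.2 | 528 | 4.4 |

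A rule based on volume also handles reduced doses: at 50% the volumes are 180 to 264 mL and the rates 1.5 to 2.2 mL/min.

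Before the change, the sponsor and pharmacy should confirm that these rates are acceptable given the animal acute-toxicity rationale. If they intend the slow rate, keep it and instead change the 2-hour duration in Tables 5-1 and 6-1 and the MTD justification in Section 6.1.

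The cost is one corrected sentence and a short table after that confirmation. No extra patients are needed.

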## 7.6 Request for CPI-613

CPI-613 must be requested from Cornerstone by the Principal Investigator (or authorized designees). CPI-613 may not be used outside the scope of this protocol, nor can it be transferred or licensed to any party not participating in this clinical study. Cornerstone policy requires that CPI-613 be shipped directly to the institution where the patient is to be treated. Cornerstone does not permit the transfer of CPI-613 between institutions (unless with prior written approval from Cornerstone). Requests must be submitted to Cornerstone by fax or email to the following address:

[name]

Department of Regulatory and Clinical Affairs

Cornerstone Pharmaceuticals, Inc.

[name]

[name]

[contact]

Telefax: [contact]

Email: [contact]

The following information must be provided in the request of CPI-613 from Cornerstone:

- Names of the principal investigator and the requestor (if different)

- Name of the study site

- Name of the pharmacist responsible for receiving and storing CPI-613

- Name of the person and address where CPI-613 is to be shipped to

- Amount (# vials) requested

- Date of request

- Date shipment expected

- Study Protocol (title and protocol#) for which the requested CPI-613 is to be used

## 7.7 Procurement of Investigational Drug

Relevant regulations require investigators to establish a record of the receipt, use and disposition of all investigational products. Investigators may delegate responsibility of drug ordering, storage, accountability and preparation to their designees.

The investigator, or the designee, will be responsible for dispensing and accounting of CPI-613 provided by Cornerstone and for exercising accepted medical and pharmacy practices.

Records of inventory, dispensation and disposition (vials received, source and dates) must be maintained. In addition, all doses dispensed should be accounted for by recording the date, study number and name, patient identification, patient initials, patient medical record number and balance forward. These records must be maintained and kept at the study site, and will be reviewed by Cornerstone, or its designee, during periodic monitoring visits.

## 7.8 Disposal of CPI-613

The following procedures are to be taken in disposal of CPI-613:

- During the study, store the used CPI-613 vials (which must be separate from the unused CPI-613 vials) at room temperature in an access-limited area. Alternatively, destroy the used CPI-613 vials according to institutional policy after documentation of the number of used CPI-613 vials and remaining volume in each used vial.

- At the end of the study, deface the label (both used and unused vials) with a permanent marking pen.

- For used CPI-613 vials (if not already destroyed according to institutional policy), after documentation of the number of used CPI-613 units and remaining volume in each container, the used containers should be destroyed at the site according to the institutional procedures for destroying toxic chemicals. A certificate documenting the destruction of used vials must be kept on file.

- All unused CPI-613 vials must be destroyed according to the policy of the institution. The destruction of CPI-613, and the quantity destroyed, must be documented. A copy of the Certificate of Destruction should be sent to:

[name]

Department of Regulatory and Clinical Affairs

Cornerstone Pharmaceuticals, Inc.

[name]

[name]

[contact]

Telefax: [contact]

Email: [contact]

## 7.9 Calculation of the Amount of CPI-613 for Each Patient

The amount of CPI-613 at each dose level is based on the BSA of the patient. The BSA values will be calculated based on the height and body weight taken during screening and this BSA value is used throughout the study. This is unless there is a >10% change in the body weight from baseline during the study. At that point, BSA should be revised based on the new body weight and height. The new BSA values will be used from that point on for the remainder of the study, unless there is another >10% change in body weight which will require another revision of the BSA.

## 7.10 Concomitant Medications and Prophylactic Treatment

Patients cannot receive any standard or investigational treatment (except CPI-613) for their cancer, or any other investigational drugs for any non-cancer indications, while on this study. All otherwise permitted concomitant medications (including trade and generic names, dosage and dosing schedule) must be recorded. Treatment of disease-related symptoms (such as nausea) is permitted. Medications administered in such instances will be considered concomitant medications and should be documented accordingly.

Prophylactic treatment for drug-related symptoms is not planned, or it will interfere with the assessment of the toxicity of the investigational product. However, following the evaluation of the causal relationship of the symptom(s) to the study drug and the information has been documented, the investigator may prescribe supportive treatment. Supportive treatment may include anti‑emetic, anti‑diarrhea, anti‑pyretic, anti‑allergic, anti‑hypertensive medications, analgesics, antibiotics, allopurinol, and others such as blood products and bone marrow growth factors. Patients may use erythropoietin for chronic anemia. Also, the hemoglobin should be maintained ≥8 g/dL during the course of the study. The treating physician may utilize erythropoietic factors, or blood or platelet transfusions at their discretion.

# 8.0 ADVERSE EVENTS LIST AND REPORTING REQUIREMENTS

## 8.1 Adverse Event Characteristics

- **CTCAE term (AE description) and grade:** The CTEP Active Version of the NCI Common Terminology Criteria for Adverse Events (CTCAE 4.0) will be utilized for AE reporting.  The CTEP Active Version of the CTCAE is identified and located on the CTEP website at (<http://ctep.cancer.gov/protocolDevelopment/electronic_applications/ctc.htm>.  All appropriate treatment areas should have access to a copy of the CTEP Active Version of CTCAE.
- **‘Expectedness’**: AEs can be ‘Unexpected’ or ‘Expected’ (see Section 7.1 above) for expedited reporting purposes only.
- **Attribution** of the AE:
  - Definite – The AE *is clearly related* to the study treatment.
  - Probable – The AE *is likely related* to the study treatment.
  - Possible – The AE *may be related* to the study treatment.
  - Unlikely – The AE *is doubtfully related* to the study treatment.
  - Unrelated – The AE *is clearly NOT related* to the study treatment.

**List of Adverse Events to be Reported:**

*Abdominal pain

*Alkaline phosphatase

*ALT (SGPT)

*Anorexia

*AST (SGOT)

*Bilirubin (hyperbilirubinemia)

*Calcium (hypercalcemia, hypocalcemia)

*Creatinine

*Diarrhea

*Flushing

*Hemoglobin (anemia)

*Injection site Reaction

*Leukocytes

*Lymphopenia

*Nausea

*Neutrophils (neutropenia)

*Platelets (thrombocytopenia)

*Potassium

*Sodium

*Vomiting

All adverse events should be reported in the AE reporting log (Appendix C) and in ORIS regardless of whether they are on this list. Asterisk (*) denotes expected Adverse Events.

All Serious Adverse Events (SAEs) which are Possibly, Probably or Definitively Related to CPI-613, and Unexpected are required to be reported to Cornerstone Pharmaceuticals via the provided SAE Reporting Form within 7 days. All completed forms must be sent to [name] at Cornerstone. Cornerstone will submit any applicable SAEs to the FDA.

SAE reports must be submitted to Cornerstone by fax or email to the following address:

Department of Regulatory and Clinical Affairs

Cornerstone Pharmaceuticals, Inc.

[name]

[name]

[contact]

Telefax: [contact]

Email: [[contact]](mailto:[contact])

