# 7.0 STUDY DRUG - CPI-613

## 7.1 Description of CPI-613 Drug Product

CPI-613 is provided in 10-mL amber glass vials. Each vial contains 10 mL of CPI-613 at a concentration 50 mg/mL, equivalent to 500 mg of CPI-613. The drug product of CPI-613 is a clear and colorless solution that is free of any particulate matter.

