**STRC notification responsibilities of the person handling the reporting/documenting of the SAE:**

1. Make a phone call to the appropriate clinical member of the STRC as listed below (page if necessary)—see note 2 below
2. Submit the STRC Notification Form WITHIN 24 HOURS of first knowledge of the event. This form is found at either the ORIS main menu page or by going to <http://ccc.wfubmc.edu/oris/strc.aspx>.

This will ensure that all persons that the event applies to will be notified; remember to file a copy of your confirmation. (Form instructions will walk you through the required fields, consult the help page for further instructions.)

1. Ensure that you document that the appropriate persons on the STRC has been contacted.
2. Follow up with/update the clinical member of STRC regarding any new developments or information obtained during the course of the SAE investigation and reporting process.

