**Elements needed to complete the electronic STRC form:**

1. ORIS Patient ID (PID)
2. Name of STRC Clinician notified/Date/Time/Comments.
3. Grade of event.
4. Is this related to protocol intervention or treatment?
5. Is suspension of the protocol needed?
6. Is any change to consent or protocol needed?
7. Was the nature or severity of the event unexpected?
8. Date of the event.
9. Brief description of the event using approved CTC version terminology.
10. Date of last study dose before event.
11. Relevant tests/labs.
12. **Most importantly make sure that the Investigator assigns attribution to the reported event (grade) using the appropriate CTCAE version for the protocol.**

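### A serious drug-related event under any of the 20 listed terms need not be reported to Cornerstone at any grade, because the list of expected events has no severity limit

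*Protocol*

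**What the plan says.** Section 8.1 classifies each adverse event as expected or unexpected and says where to look and what the classification is for: "see Section 7.1 above) for expedited reporting purposes only". The section referred to, 7.1, is the description of the drug product and opens with "CPI-613 is provided in 10-mL amber glass vials".

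The list headed "List of Adverse Events to be Reported" then gives the terms, with the key "Asterisk (*) denotes expected Adverse Events". Below it stands the rule for the supplier: "All Serious Adverse Events (SAEs) which are Possibly, Probably or Definitively Related to CPI-613, and Unexpected are required to be reported to Cornerstone Pharmaceuticals", within 7 days. The same paragraph adds "Cornerstone will submit any applicable SAEs to the FDA".

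Section 8.2 and Appendix B set a separate institutional rule: unexpected Grade 4 events and all Grade 5 events go to the STRC. Among the items on the STRC electronic form is the question "Was the nature or severity of the event unexpected".

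**The concern.** Expectedness is one of the conditions for a report to Cornerstone, yet the protocol does not say how severity bears on it. The cross-reference gives no definition, so a reader is left with the asterisks. These attach to bare terms, several of which can be serious or life-threatening in their severe forms: neutrophils, platelets, hemoglobin, potassium, sodium, calcium, creatinine.

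At stake is whether the party that makes the FDA submissions must be told of the severe forms of the toxicities already associated with the drug. Section 7.2 says that the drug's toxicity in humans is not fully understood. Section 6.1 treats patients at the maximum tolerated dose from Phase I. In that setting an unusually severe case of a known toxicity is informative, and the rule as worded does not require it to be sent.

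**Working it through.** No formula applies and the protocol gives no figure to reproduce. The check is a count, followed by applying the rules to one type of case.

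**Count of the list (Section 8.1).** Terms: abdominal pain, alkaline phosphatase, ALT, anorexia, AST, bilirubin, calcium, creatinine, diarrhea, flushing, hemoglobin, injection site reaction, leukocytes, lymphopenia, nausea, neutrophils, platelets, potassium, sodium, vomiting. That is 20 terms. With an asterisk: 20 of 20. With a grade or severity limit: 0 of 20.

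**Rules applied.**
- Cornerstone (Section 8.1): a report is required if the event is serious, at least possibly related, and unexpected. All three must hold.
- STRC (Section 8.2; Appendix B, Table 1): Grades 1 to 3 are not required; Grade 4 is required only if unexpected; Grade 5 is always required. In the expected Grade 4 column, 5 of 5 attribution rows are marked as not required, including the row for definite attribution.

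**Case: a serious event at least possibly related to CPI-613.** A listed term is taken as expected and an unlisted one as unexpected.

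| Grade | Listed, to Cornerstone | Listed, to STRC | Unlisted, to Cornerstone | Unlisted, to STRC |
| --- | --- | --- | --- | --- |
| 1 to 3 | not required | not required | required | not required |
| 4 | not required | not required | required | required |
| 5 | not required | required | required | required |

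For a listed term, a Cornerstone report is required in 0 of the 3 grade bands; for an unlisted term, in 3 of 3. At Grade 4 a listed term has a required report to neither body.

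**Does other text close the gap?**
- The severity question is on the STRC form only. Appendix B says that each entity has its own reporting rules, so it does not amend the Cornerstone rule.
- Table 1 has expected columns at Grades 4 and 5. The protocol therefore recognises an event that is life-threatening or fatal and still expected.
- IRB reporting (Section 8.3), the adverse event log and the ORIS database are not described as routes to Cornerstone.
- Cornerstone's monitoring visits (Section 7.7) are tied to drug accountability records.

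**An illustration from the protocol's own safety focus.** Section 6.2 has separate rules for creatinine elevation and suspends enrollment for Grade 3 or 4 acute renal failure possibly related to the drug. Creatinine is on the expected list; acute renal failure is not. Whether Cornerstone must be told of a severe renal event can therefore depend on which term is recorded.

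**The case against.** The strongest reply is that the protocol does not say that a listed term is expected at every grade. It is silent on severity, and the one place that raises severity, the STRC form, treats it as relevant. An investigator could reasonably class an unusually severe listed event as unexpected and report it. This stands in part: expectedness at any grade is the effect of an ungraded list, not an explicit statement. But the reporting duty then rests on a reading that the Cornerstone rule does not contain.

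The reach is also limited. Serious events under unlisted terms are reported if at least possibly related. Grade and seriousness are separate fields on the adverse event log, so a Grade 4 laboratory value is not automatically a serious event. Both limits stand; the routing above is for events that meet the seriousness test.

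A reader might infer more than the text supports:
- *That such events never reach Cornerstone.* The rule sets what is required and does not bar a voluntary report.
- *That expectedness decides all urgent reporting.* All Grade 5 events go to the STRC regardless, and the IRB rule is framed by unanticipated problems and institutional policy, not by the asterisk.
- *That nobody beyond the site would see a cluster.* The protocol does not say what else Cornerstone receives, and the data safety monitoring plan it mentions is not shown.
- *That 7 days for Cornerstone conflicts with the STRC instruction, "Submit the STRC Notification Form WITHIN 24 HOURS of first knowledge of the event".* These are different recipients under separate rules.
- *That leaving out events judged unlikely or unrelated is an error.* It is a stated choice that contradicts nothing else in the protocol.

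**Conclusion.** The point holds as a defect in a stated rule. All 20 listed terms are expected without a severity limit, the definition of expectedness has a dead reference, and Cornerstone must be sent only events that are both related and unexpected. A serious related event under a listed term is therefore not required to reach Cornerstone at any grade; at Grade 4 it is not required to reach the STRC either.

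This rests on two assumptions: that the asterisked list is the working definition of expectedness, since Section 7.1 offers none, and that the event meets the seriousness test. How many such events would occur in 20 patients cannot be estimated from the protocol, which gives no event rates by grade. The change should be made, because it costs little and concerns safety reporting; it does not affect the efficacy estimates.

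**What to change.** Three wording changes to Section 8.1:

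1. In the Cornerstone rule, strike the condition that the event be unexpected, so that every serious adverse event at least possibly related to CPI-613 is sent. Cornerstone can then judge which of these are applicable for FDA submission.
2. Replace the reference to Section 7.1 with a reference to the adverse event list in Section 8.1.
3. State that a listed event of unexpected severity counts as unexpected for STRC reporting, in line with the question already on the STRC form.

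A grade ceiling for each term would be sharper than the third change, but it needs Phase I data by grade that the protocol does not give; Section 1.2 says only that the drug was well tolerated at doses up to 3,000 mg/m². No change to IRB reporting is needed.

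The cost is a protocol amendment and a few more serious adverse event forms for 20 patients, with a small added review load at Cornerstone.
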